### Study management

The study is overseen by the Catalysing uptake of under‐utilised tools & treatment simplification for HepC (CUTTS HepC) project steering committee, convened by Médecins du Monde with at least one representative from each Consortium partner organisation. Study data management, study monitoring and independent monitoring are managed by Burnet. Relevant study investigators and data manager/statistician will have access to the final dataset. Access to the final dataset will otherwise be managed on request on a case-by-case basis.

### Ethical review

This study has undergone external scientific peer review and been approved by the Alfred Hospital Ethics Committee (Project #618/23, Project #340/24, Project #351/24), WHO Ethics Review Committee (ERC.0004066, ERC.0004123, ERC.0004276, ERC.0004257) and country-specific ethics committees (Armenia NCID Ethics Committee, Georgia Health Research Union, Tanzania NatHREC). Any amendments to the protocol will be communicated to relevant committees and investigators.

Informed consent will be obtained from all participants prior to enrolment. Potential participants will be presented with detailed information about the study procedures, objectives, risks and benefits; the consent form is provided in online supplemental material 4. Participants will be able to refuse or terminate participation at any time. Participants will be reimbursed US$4–US$10 at their baseline visit and US$4–US$10 for their SVR visit, for completion of the survey. Participants will be reimbursed US$30 for interview participation in Armenia and Georgia, and US$10 for interview participation in Tanzania. Reimbursement will be by cash in local currency. In Tanzania, participants attending Mukikute will also receive transportation support of US$1–US$4 for study visits (apart from when baseline and SVR questionnaire is completed during the study visit).

#### Data management

Online supplemental material 3 provides detailed description of data collected in each CRF and the participant survey questionnaire.

Data will be entered into and managed in Research Electronic Data Capture (REDCap), hosted and managed by Burnet Institute in Australia. REDCap is a secure web platform for building and managing online databases and surveys for research. In adherence to the European Union General Data Protection Regulation requirements, names and contact information will be securely stored in-country and will not be recorded in REDCap.

All CRFs and surveys are available in paper format in case of power or internet outage and will be stored securely at study sites.

Regular fortnightly data quality checks will be conducted throughout the study implementation period to ensure high-quality data. Quarterly site monitoring visits will also be conducted.

Quantitative data analysis will be performed in Stata SE V.17, the R Programming Language or equivalent analysis programme. Qualitative data analysis will be performed in NVivo, or other equivalent analysis programme and visualised using Lucidchart or equivalent programme.

### Adverse events and reporting

This study uses a drug with side effects that are already known.^49^ However, the study will trial a modified clinical pathway outside of current guidelines for HCV treatment in arm 2, that is, starting participants onto treatment drug without confirmation of HCV RNA status (current HCV infection) and without receipt of liver function and platelets investigation results to complete cirrhosis assessment.

It will therefore report adverse events that, in the opinion of the investigator, are not deemed to be expected or are increased in severity from prior observations. Adverse events considered related to the study drug administration will be captured up to 24 weeks after the last recorded study drug dose.

Burnet Institute, with Médecins du Monde as the study sponsor, is responsible for reporting adverse events and protocol modifications to Data Safety Monitoring Board and to the relevant Ethics Committees, where appropriate.

### Data monitoring

The trial will be monitored by an independent data safety and monitoring board with an independent statistician, clinical experts and community representatives, with at least one representative from each implementing country. There will be predefined periodic analysis if the data safety and monitoring board is concerned about any of the safety end points (serious adverse events, proportion ‘over-treated’, treatment failures).

Access to de-identified data will be limited to study investigators. The Data Safety Monitoring Board terms of reference were included in the ethics applications.

### Dissemination

The results from this study will be published and presented as peer-reviewed publications, lay summary reports (English and local languages), conference presentations, dissemination workshops with key stakeholders and with communities of people affected by HCV through relevant organisations/networks. Summary reports will be available on the Burnet Institute website, INPUD website, the Médecins du Monde website and at study sites. Results may also form part of PhD, Masters or Honours student theses. Authorship for publications arising from this study will adhere to Consortium authorship and publication policy, and the International Committee of Medical Journal Editors guidelines. The study protocol will be accessible via publication, and a full statistical analysis plan will be accessible as online appendix on the trial’s registration record.

All published quantitative and qualitative data will be non-identifiable aggregate data.

### Project timeline

Participant enrolment will close once the treatment initiation target has been met or by June 2026 (whichever is earlier). This allows sufficient time for enrolment and follow-up (minimum 6 months). The study will close in December 2026, or earlier if targets are met earlier.

The study opened recruitment in Armenia in October 2024, in June 2025 in Georgia and in August 2025 in Tanzania. Implementation is intended to continue up until December 2026.

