**Methods and analysis:**

This study is a multi-country non-randomised, quasi-experimental, prospective comparative two-arm trial. It aims to assess the feasibility of implementation, retention in hepatitis C care and achievement of cure and cost-effectiveness outcomes, comparing two simplified hepatitis C testing and treatment pathways.

Arm 1 is a standard simplified test and treat model of care following global guidance, and arm 2 is an innovative rapid, same-day treatment initiation model of care using a presumptive treatment approach based on shortened read-time of the point-of-care OraQuick hepatitis C antibody test result. Secondary outcomes include assessing the accuracy of the OraQuick hepatitis C antibody test in predicting viraemia and the acceptability of each pathway.

This study will be implemented in Armenia, Georgia and Tanzania. Treatment-naïve people who inject drugs aged over 18 years in each country will be eligible for enrolment.

Recruitment commenced in October 2024 in Armenia, June 2025 in Georgia and August 2025 in Tanzania and is anticipated to close by December 2026.

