### Treatment outcome assessment (SVR weeks 4–20)

Participants will attend the study clinic to have venous blood samples taken for RNA testing to confirm if they have achieved SVR post-treatment.Participants can be assessed for SVR anytime from ≥4 weeks post-treatment completion until 20 weeks post-treatment completion*.Participants will complete the interviewer-administered SVR participant questionnaire, covering similar domains to the baseline questionnaire.

SVR will be defined as ‘HCV VL <10 IU/mL’ or ‘HCV VL Not Detected’, if using GeneXpert HCV VL test/other quantitative test, and as ‘HCV RNA not detected’, as per laboratory procedures if using another HCV RNA test.

*In secondary analyses, if an RNA negative result is returned after 20 weeks, it will be categorised as achieving SVR. If a positive result is returned after 20 weeks, the participant will be categorised as ‘indeterminate SVR’, given the uncertainty regarding whether treatment was unsuccessful or the participant had been re-infected with hepatitis C.

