### Study exit

Participants may exit the study at various time points: when they choose to withdraw from the study, when the clinician identifies a medical issue/ineligibility prompting participant withdrawal or when they have been identified as lost to follow-up due to no longer being contactable.

Throughout, there will be a minimum of three attempts over up to 3 weeks to contact participants to arrange the follow-up appointment if the participant misses the scheduled appointment. In the case of SVR, participants will remain in the study until the SVR20 time point passes; they will be contacted up to four times, every 4 weeks to attempt to arrange for SVR appointment.

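### The stated minimum of 6 months' follow-up is shorter than the plan's own SVR and adverse-event windows, and the shortfall would fall mainly on late arm 2 starters

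*Protocol article*

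**What the plan says.** All references are to the protocol article.

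- **Project timeline.** "Participant enrolment will close once the treatment initiation target has been met or by June 2026 (whichever is earlier"). It goes on: "This allows sufficient time for enrolment and follow-up (minimum 6 months"). Then: "The study will close in December 2026, or earlier if targets are met earlier".
- **Abstract, Methods and analysis.** Recruitment "is anticipated to close by December 2026".
- **Intervention.** The treatment course is 12 weeks.
- **Treatment outcome assessment.** SVR may be assessed from 4 weeks after treatment "until 20 weeks post-treatment completion".
- **Study exit.** For SVR, "participants will remain in the study until the SVR20 time point passes". Up to four contacts, 4 weeks apart, are made to arrange the visit.
- **Adverse events and reporting.** Drug-related events are "captured up to 24 weeks after the last recorded study drug dose".
- **Trial study design.** In each country arm 1 is enrolled to its treatment target, then arm 2. Enrolment closes on arm 2.
- **Assessing outcome 1.** Cure is the proportion achieving SVR among those prescribed treatment.

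**The concern.** The timeline calls 6 months sufficient, but the SVR and adverse-event rules each run longer than that once the treatment course is added. The participants affected are the last to start. With consecutive enrolment these are, in the expected course of events, arm 2 participants. Arm 1 would then have the whole SVR window and every contact attempt, while part of arm 2 would not.

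Cure is a primary outcome with everyone prescribed treatment in its denominator. As written, a participant with no SVR result cannot count as a success. The sample size section expects equal cure in both arms (about 95%), so even a small gap in ascertainment could look like a difference between arms. Covariate adjustment cannot recover tests that were never taken. Adverse-event follow-up would also be shortened in the arm that, by the protocol's own account, works outside current guidelines.

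**Working it through.** **1. The plan's own figure.** June to December 2026 is 6 months: 6 × 30.4375 / 7 = 26.1 weeks. The stated minimum reproduces.

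**2. What the rules require, from first dose.**
- SVR window opens: 12 + 4 = 16 weeks.
- SVR window closes: 12 + 20 = 32 weeks.
- Adverse-event capture ends after a full course: 12 + 24 = 36 weeks.

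Extra treatment weeks after missed doses, which the Visit 3 section allows, would lengthen these.

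**3. What the calendar allows.** The documents give months, not days, so the range is shown.

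| Last start | Study close | Weeks available | Post-treatment weeks (minus 12) |
|---|---|---|---|
| 1 June | 31 December | 30.4 | 18.4 |
| 30 June | 31 December | 26.3 | 14.3 |
| 30 June | 1 December | 22.0 | 10.0 |

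No combination reaches 32 or 36 weeks. All of them exceed 16.

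**4. Last start dates that fit.**
- Close on 31 December 2026: minus 32 weeks = 21 May 2026; minus 36 weeks = 23 April 2026.
- Close on 1 December 2026: 21 April and 24 March 2026.
- For a 30 June 2026 starter: plus 32 weeks = 9 February 2027; plus 36 weeks = 9 March 2027.

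**5. Contact attempts.** If the first is made at post-treatment week 4 (an assumption), the four fall at weeks 4, 8, 12 and 16. A 30 June starter loses the last one with a 31 December close (14.3 weeks) and the last two with a 1 December close (10.0 weeks).

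**6. Which arm.** No arm-switch dates are given. Assume recruitment from the first of each stated opening month to 30 June 2026, split equally in time between the arms. Arm 1 then ends about August 2025 in Armenia, December 2025 in Georgia and January 2026 in Tanzania, before every cut-off in step 4. The share of arm 2 starting too late for the full window, for a close between 31 and 1 December, is:

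| Country | Full SVR window | Full adverse-event window |
|---|---|---|
| Armenia | 13–22% | 21–31% |
| Georgia | 20–36% | 35–50% |
| Tanzania | 24–42% | 41–59% |

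Weighted by the arm 2 targets in table 3 (115, 120, 115), the SVR shares are:
- Low: (0.13 × 115 + 0.20 × 120 + 0.24 × 115) / 350 = 66.55 / 350 = 19%.
- High: (0.22 × 115 + 0.36 × 120 + 0.42 × 115) / 350 = 116.8 / 350 = 33%.

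**7. Possible effect on cure (illustration only).** The share of SVR tests that would have been taken in the lost part of the window is not in the documents. At 5%, arm 2 cure falls by at most 0.05 × 19% to 0.05 × 33% = 1.0 to 1.7 points. At 10% it falls by at most 1.9 to 3.3 points. These are upper limits, because many of those affected lose only a few days or weeks of the window.

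**The case against.** The strongest reply is that week 20 is the end of a permitted window, not a required visit. One test at any time from post-treatment week 4 is enough, and even the shortest calendar reading reaches week 10. A reader might infer that late starters cannot have their outcome measured; the documents do not support that. Only people who would have missed the early part of the window and attended later are lost. This stands, and it is why the effect is probably modest. It does not remove the conflict, because the Study exit section keeps participants in until week 20 has passed.

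A reader might also infer that arm 2 alone is affected by design. That goes too far. If a country were still enrolling arm 1 in spring 2026, arm 1 would be cut too. June 2026 is also an outer limit, since enrolment may close sooner on target.

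A third tempting reading concerns results after week 20: "if an RNA negative result is returned after 20 weeks, it will be categorised as achieving SVR", while late positives become indeterminate, so late results could add cures but not failures, mainly in arm 1. The protocol confines this to secondary analyses, gives a reason (failure cannot be told from reinfection) and does not state the denominator. It does not bear on the primary cure comparison.

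On safety, adverse-event capture runs up to 24 weeks with no visit scheduled for it, and SVR retention ends at week 20 for everyone, so weeks 20 to 24 are not a gap peculiar to late starters. RNA-negative arm 2 participants who stop within the first 28-day supply need about 4 + 24 = 28 weeks, not 36.

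Finally, the abstract's December date could be loose wording for the end of the study. Taken literally, anyone starting after 10 September 2026 could not reach even post-treatment week 4 by 31 December. The specific June rule in the Project timeline makes that an inconsistency to correct rather than a likely plan.

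**Conclusion.** The contradiction holds on every calendar reading. At most 30.4 weeks are available to the latest starters, against 32 weeks for the SVR window and 36 for adverse-event capture after a full course. At 6 months (26.1 weeks) the shortfall is about 6 and 10 weeks. The June and December recruitment dates also conflict.

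The participants affected would be mainly late arm 2 starters, provided that arm 1 closes in each country before spring 2026. With equal enrolment time per arm, about 19–33% of arm 2 would lose some of the SVR window. They would lose its later part, up to two contact attempts and late adverse-event capture, but not the chance of being tested.

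This could lower observed arm 2 cure somewhat for calendar reasons alone. The size cannot be derived from the documents. How missing SVR results are handled may be settled in the statistical analysis plan, which is not shown. It cannot mend the dates, which are fixed here.

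**What to change.** Reconcile the abstract, Study exit, Adverse events and Project timeline sections so that one recruitment close and one data-collection close are consistent with the SVR and adverse-event windows. Either:

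- **Bring the last treatment start forward.** For a 31 December 2026 close this means 21 May 2026 for the full SVR window and 23 April 2026 for adverse events. The first date alone does not cover the second.
- **Extend follow-up data collection.** For a 30 June 2026 starter this means to about 9 February 2027 for SVR and 9 March 2027 for adverse events.

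If neither date can move, replace the sufficiency statement with the follow-up actually available. Compare cure between arms on a common post-treatment window that the last starter can complete, with the full 4–20 week window as a sensitivity analysis. Set its upper limit from the actual closing dates: about week 14 for 30 June to 31 December, but only week 10 if the study closes on 1 December. The handling of indeterminate late results need not change for this purpose.

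The cost is a protocol amendment notified to the ethics committees and, under the common window, the loss of some late arm 1 results from the main comparison. An earlier last start may also cost some arm 2 recruitment.

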## Discussion

The outcomes from both models of care are integral to supporting the national response to hepatitis C across the three implementing countries.

First, country-specific feasibility, acceptability, effectiveness and cost-effectiveness evidence is important to support scaled-up implementation and decentralisation of the simplified care model in Armenia and Tanzania specifically. Preparatory work for the study has further simplified the care model in Georgia for all harm reduction sites by removing the requirement for on-treatment monitoring.

Second, the utility of the 5 min read-time component to support same-day treatment initiation will be dependent on the impact on linkage to treatment, the proportion overtreated and the relative cost-effectiveness of this strategy. The potential utility will also differ across countries based on background prevalence and incidence of HCV, and treatment rates, and the relative cost of HCV RNA tests compared with HCV treatment.

While we are evaluating the feasibility and scale-up requirements of these models of care to inform future scale-up, the implementation as part of a research study with relatively few participants compared with national programmes limits its direct replicability for scaled-up implementation.

The outcomes of this study will support the ongoing decentralisation and scaled-up implementation of national hepatitis C response in the three implementing countries and provide evidence to support efforts in other LMICs.
